##### **Survival**

Time to survival will be computed from the date of enrollment to the date of death for any reason or censored at the date of the last contact, whichever occurs earlier.

#### **9.2.2 Safety Analysis**

The safety analysis will be conducted on the Intention to Treat (ITT) population.

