### **5.2 Secondary Outcomes**

- ORR at the end of cycle 6 (defined according to 2014 Lugano criteria and 2016 Refinement of the Lugano Classification lymphoma response criteria in the era of immunomodulatory therapy)
- 2-year progression free survival
- 2-year overall survival
- Duration of response
- EBV-DNA load change
- Rate of adverse events coded according to CTCAE ver 4.0
- QoL
- Treatment-related mortality

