### **7.5 Management and monitoring of AEs**

Dose modifications: there will be no dose modifications in this study. Patients with severe chemotherapy toxicity or patients who delay chemotherapy for more than 2 weeks due to adverse events are recommended to withdraw from the study.

Sintilimab treatment may be temporarily suspended in patients experiencing toxicity considered related to study treatment. If corticosteroids are initiated for treatment of the toxicity, the must be tapered over > 1 month to <10 mg/day or oral prednisone or equivalent before sintilimab can be resumed. If sintilimab is withheld for > 12 weeks treatment can be resumed prior approval by the principal investigator. In Table 1 is reported a guideline for the management of patients who experienced specific adverse events (see also Appendix 5).

AEs associated with sintilimab exposure may represent an immunologic etiology. These immune-related AEs (irAEs) may occur shortly after the first dose or several months after the last dose of sintilimab treatment and may affect more than one body system simultaneously. Therefore, early recognition and initiation of treatment is critical to reduce complications. Based on existing clinical study data, most irAEs were reversible and could be managed with interruptions of sintilimab, administration

of corticosteroids and/or other supportive care. For suspected irAEs, ensure adequate evaluation to confirm etiology or exclude other causes. Additional procedures or tests such as bronchoscopy, endoscopy, skin biopsy may be included as part of the evaluation. Based on the severity of irAEs, withhold or permanently discontinue sintilimab and administer corticosteroids. Dose modification and toxicity management guidelines for irAEs associated with sintilimab are provided in Table 1.

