| HBV, HCV and HIV serology                                      | X                        |                              |                           |                                |                                               |                                |                     |
| Tumor Imaging (evaluation)                                     | X                        |                              | X                         | X                              | X                                             | X                              |                     |
| EORTC QLQ-C30                                                  | X                        |                              | X                         | X                              | X                                             | X                              |                     |
| Concomitant Medications                                        | X                        | X                            | X                         | X                              |                                               | X                              |                     |
| AEs Assessment                                                 |                          | X                            | X                         | X                              |                                               | X                              |                     |
| Survival                                                       |                          |                              |                           |                                |                                               | X                              | X                   |
| Pegaspargase                                                   |                          | X                            |                           |                                |                                               |                                |                     |
| Sintilimab                                                     |                          | X                            |                           | X                              |                                               |                                |                     |

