### **8.3 Adverse Event Reporting Requirements**

#### **8.3.1 Assessment of AEs**

Subjects will be evaluated for AEs at each visit with the NCI CTCAE v4.0.

Adverse events, SAEs, and other reportable safety events will be reported by the participant (or, when appropriate, by a caregiver, surrogate, or the participant's legally authorized representative).

The investigator and any designees are responsible for detecting, documenting, and reporting events that meet the definition of an AE or SAE as well as other reportable safety events. Investigators remain responsible for following up AEs, SAEs, and other reportable safety events for outcome.

The investigator, who is a qualified physician, will assess events that meet the definition of an AE or SAE as well as other reportable safety events with respect to seriousness, intensity/toxicity and causality.

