#### **9.2.1 Efficacy Analysis**

##### **Analysis Populations**

Main and secondary study objectives will be assessed with an intent to treat analysis. (i.e. all enrolled patients)

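### Table 3 schedules no adverse-event check at the follow-up visits, against 8.3.1 and 7.5, so late immune-related events can be missed; and safety is analysed on all enrolled rather than all dosed patients

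*Protocol*

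**What the plan says.** **Collection of adverse events.** Section 8.3.1 sets a general rule: "Subjects will be evaluated for AEs at each visit with the NCI CTCAE v4.0". Section 7.5 says of immune-related events that they "may occur shortly after the first dose or several months after the last dose of sintilimab treatment". In Table 3 (Section 8.1) the row "AEs Assessment" is marked at day 1 of the induction cycles, at end of induction, at day 1 of the maintenance cycles and at end of treatment (EOT). It is blank at pre-treatment, at the maintenance Evaluation visits and at the 4-monthly follow-up (FUP) visits. At FUP only Survival is marked. Table 3 places EOT within 30 days of cycle 34. For patients who stop for progression or an adverse event, Section 6.1 places it at 30 days from the last dose, or before new anticancer therapy if that comes sooner.

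**Population.** Section 9.2.2 reads: "The safety analysis will be conducted on the Intention to Treat (ITT) population". The only definition of that population is in Section 9.2.1, under Analysis Populations: "i.e. all enrolled patients". It carries no dosing condition, and the protocol names no treated-patient set. Section 5.2 lists "Rate of adverse events coded according to CTCAE ver 4.0" and treatment-related mortality among the secondary outcomes.

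**The concern.** The protocol expects a class of events to appear after treatment ends, and its schedule has no prompt to look for them then. A site that works from Table 3 would record survival at FUP and nothing else; a site that works from 8.3.1 would assess adverse events there too. Late immune-related events would then be captured unevenly, or not at all.

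The denominator is a separate matter. A patient who is enrolled but never dosed cannot have a drug toxicity, and Table 3 schedules no adverse-event assessment before treatment, so that patient would enter the denominator with almost no chance of entering the numerator.

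Both features can only lower the reported rates. Section 4 sets out to test whether the combination is an active and safe option, and Section 3.1 calls the trial preparatory to a larger randomised study. With 22 patients, one or two misclassified patients visibly change a rate.

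**Working it through.** **Inputs.** Planned enrolment is 20 + 2 = 22 (Section 9.1). Cycles last 21 days, with 6 in induction and up to 28 in maintenance, 34 in all (Sections 7.1, 7.2 and Table 3). Follow-up runs up to 2 years, about day 730, from the last enrolment (Section 6.1). The protocol gives no figure for safety. Its only relevant number is the denominator, and that reproduces: with null rate 0.40, alternative 0.70, two-sided alpha 0.05 and power 0.80,

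n = [(1.960 × √0.24 + 0.842 × √0.21) / 0.30]² = 20.1,

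against the stated 20, or 22 with drop-offs.

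**1. The period with no scheduled adverse-event check, assuming no delays.**

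- *Patient who completes all cycles, enrolled last.* Cycle 34 day 1 is day 33 × 21 + 1 = 694. EOT is by about day 694 + 30 = 724. Follow-up ends at about day 730, so about 5 weeks (36 days) remain after the last dose and only about 6 days after EOT. Patients enrolled earlier have more.
- *Patient who stops after cycle 6, enrolled last.* Cycle 6 day 1 is day 5 × 21 + 1 = 106, and sintilimab is given on day 107. EOT is at about day 137. That leaves 730 − 137 = 593 days, about 19 months, in which the scheduled FUP visits carry Survival only. This assumes that the patient enters FUP after stopping.

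The gap is therefore longest for patients who stop early.

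**2. Size of a missed event.** If a patient's only event is a late one that goes unrecorded, the rate falls by 1/22 = 4.5 points, or by 1/20 = 5.0 points if 20 patients are analysed. Two such patients cost 9.1 to 10.0 points. The protocol gives no basis for estimating how many there would be.

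**3. Denominator.** Reported rate = rate among dosed patients × (number dosed / 22). The number undosed is an assumption:

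| Undosed | Factor | A true 50% reads |
|---|---|---|
| 0 | 1.000 | 50.0% |
| 1 | 21/22 = 0.955 | 47.7% |
| 2 | 20/22 = 0.909 | 45.5% |
| 3 | 19/22 = 0.864 | 43.2% |
| 4 | 18/22 = 0.818 | 40.9% |

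If no treatment-related deaths are seen, the exact two-sided 95% upper limit is 1 − 0.025^(1/n): 16.8% for n = 20 and 15.4% for n = 22.

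**4. Evaluation visits.** These fall 14–21 days from cycles 12, 18, 24 and 30. The next day 1 visit, where adverse events are marked, is due at 21 days. The interval is at most 21 − 14 = 7 days without delays, so the blank Evaluation cells lose almost nothing.

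**The case against.** A reader might infer that Table 3 settles the matter and adverse-event collection stops at EOT. The text does not support that. Besides 8.3.1, the AE Reporting section requires every adverse experience observed or reported to be recorded, investigators stay responsible for following up events, and all serious events on study go to the review board. None of these has an EOT cut-off. The FUP column may also be incomplete in general: imaging is blank there, although Section 6.1 schedules tumour assessments during follow-up. The table's title mentions footnotes that are not visible in the text available, and one could qualify the row. All of this stands, and it makes the point a contradiction rather than a fixed rule. It does not remove the contradiction.

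A reader might also infer that late treatment-related deaths go unrecorded. They do not: Survival is marked at FUP, overall survival counts death from any cause, and death is a serious event whose causality the investigator assesses. Only a scheduled prompt for relatedness is absent.

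On the denominator, it is fair to say that the trial may enrol nobody who goes undosed. Section 6.1 says that all eligible patients receive induction, Section 9.1 does not say when its 2 drop-offs leave, and Section 6.2.3 lists mainly reasons that arise during treatment. The dilution is therefore conditional. The stated rule is still the wrong one for the case in which it matters.

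**Conclusion.** The point holds in two parts.

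The stronger part is the conflict between Table 3, which schedules no adverse-event assessment at FUP, and Sections 8.3.1 and 7.5. Late immune-related events can be missed, at a cost of 4.5 to 5.0 points for each patient whose only event is lost. Patients who stop early and remain in follow-up are the most exposed.

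The lesser part is the choice of all enrolled patients for safety. Its effect is nil if all 22 are dosed, and a relative reduction of 4.5% with one undosed patient or 9.1% with two.

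It would go too far to conclude that toxicity will be understated. The number of late events is unknown, the number of undosed patients may be zero, and the text outside Table 3 could lead sites to collect the events anyway. What can be said is that any error runs towards understatement. Neither part is a detail left for a statistical analysis plan: the protocol itself states the population and the schedule.

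**What to change.** 1. In Table 3, mark adverse-event assessment at the existing FUP visits, covering at least immune-related events, serious events and the relatedness of deaths, so that the table agrees with 8.3.1.
2. State how long after the last dose adverse events are collected, in line with 7.5. This needs its own sentence: as shown above, a late-enrolled patient who completes all cycles may reach the end of follow-up before a first 4-monthly visit.
3. In 9.2.2, define the safety set as all patients who received at least one dose of pegaspargase or sintilimab. Section 9.2.1 assigns all secondary objectives, which include safety, to the enrolled population, so it needs a matching exception.

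The cost is wording plus one case-report item at visits already scheduled. Reported adverse-event rates may read slightly higher.

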## APPENDIX 1 - REVISED CRITERIA FOR RESPONSE ASSESSMENT

(2014)

| Response and site                                                                                                                                                  | PET-CT based response                                                                                                                                                                                                                                                                                                                                                                                                                                                                                                                                                                                                                                                                               | CT-Based response                                                                                                                                                                                                                                                                                                                                                                                                                                                                                    |
|--------------------------------------------------------------------------------------------------------------------------------------------------------------------|-----------------------------------------------------------------------------------------------------------------------------------------------------------------------------------------------------------------------------------------------------------------------------------------------------------------------------------------------------------------------------------------------------------------------------------------------------------------------------------------------------------------------------------------------------------------------------------------------------------------------------------------------------------------------------------------------------|------------------------------------------------------------------------------------------------------------------------------------------------------------------------------------------------------------------------------------------------------------------------------------------------------------------------------------------------------------------------------------------------------------------------------------------------------------------------------------------------------|
| Complete

Lymph nodes and extralymphatic sites

Non measured lesions
Organ enlargement
New lesions
Bone marrow | Complete metabolic response

Score 1, 2, or 3* with or without a residual mass on 5PS†
It is recognized that in Waldeyer's ring or extranodal sites with high physiologic uptake or with activation within spleen or marrow (e.g., with chemotherapy or myeloid colony-stimulating factors), uptake may be greater than normal mediastinum and/or liver. In this circumstance, complete metabolic response may be inferred if uptake at sites of initial involvement is no greater than surrounding normal tissue even if the tissue has high physiologic uptake.

Not applicable
Not applicable
None
No evidence of FDG-avid disease in marrow                      | Complete response (all of the following)

Target nodes/nodal masses must regress to ≤ 1.5 cm in LDI.
No extralymphatic sites of disease.

Absent
Regress to normal
None
Normal by morphology; if indeterminate, IHC negative                                                                                                                                                                                                                  |
| Partial

Lymph nodes and extralymphatic sites

Non measured lesions
Organ enlargement
New lesions
Bone marrow  | Partial metabolic response

Score 4 or 5 † with reduced uptake compared with baseline and residual mass(es) of any size.
At interim, these findings suggest responding disease.
At end of treatment, these findings indicate residual disease.

Not applicable
Not applicable
None
Residual uptake higher than uptake in normal marrow but reduced compared with baseline (diffuse uptake compatible with reactive changes from chemotherapy allowed). If there are persistent focal changes in the marrow in the context of a nodal response, consideration should be given to further evaluation with MRI or biopsy or an interval scan | Partial remission (all of the following)

≥50% decrease in SPD of up to 6 target measurable nodes and extranodal sites
When a lesion is too small to measure on CT, assign 5 mm x 5 mm as the default value.
When no longer visible, 0 x 0 mm
For a node > 5 mm x 5 mm, but smaller than normal, use actual measurement for calculation.
Absent/normal, regressed, but no increase
Spleen must have regressed by ≥50% in length beyond normal.
None
Not applicable |
| No response or stable disease

Target nodes/nodal masses, extranodal lesions                                                                          | No metabolic response

Score 4 or 5 with no significant change in FDG uptake from baseline at interim or end of treatment                                                                                                                                                                                                                                                                                                                                                                                                                                                                                                                                                              | Stable disease

>50% decrease from baseline in SPD of up to 6 dominant, measurable nodes and extranodal sites; no criteria for progressive disease are met                                                                                                                                                                                                                                                                                                                              |

|                                                                                                                                                                                                                                                                                                                                                                                                                                                                                                                                                                                                                                                                                                                                                                                                                                                                                                                                                                                                                                                                                                                                                                                                                                                                                                                                                                                                                                                                                                                                                                                                                                                                                                                                                                                                                                                                                                                                                                                                                                                                                                                                                                                                                                                                                                                                                                                                                                                                                    |                                                                                                                                                                                                    |                                                                                                                                                                                                                                                                                                                                                                                                                                                                            |
|------------------------------------------------------------------------------------------------------------------------------------------------------------------------------------------------------------------------------------------------------------------------------------------------------------------------------------------------------------------------------------------------------------------------------------------------------------------------------------------------------------------------------------------------------------------------------------------------------------------------------------------------------------------------------------------------------------------------------------------------------------------------------------------------------------------------------------------------------------------------------------------------------------------------------------------------------------------------------------------------------------------------------------------------------------------------------------------------------------------------------------------------------------------------------------------------------------------------------------------------------------------------------------------------------------------------------------------------------------------------------------------------------------------------------------------------------------------------------------------------------------------------------------------------------------------------------------------------------------------------------------------------------------------------------------------------------------------------------------------------------------------------------------------------------------------------------------------------------------------------------------------------------------------------------------------------------------------------------------------------------------------------------------------------------------------------------------------------------------------------------------------------------------------------------------------------------------------------------------------------------------------------------------------------------------------------------------------------------------------------------------------------------------------------------------------------------------------------------------|----------------------------------------------------------------------------------------------------------------------------------------------------------------------------------------------------|----------------------------------------------------------------------------------------------------------------------------------------------------------------------------------------------------------------------------------------------------------------------------------------------------------------------------------------------------------------------------------------------------------------------------------------------------------------------------|
| Nonmeasured lesions                                                                                                                                                                                                                                                                                                                                                                                                                                                                                                                                                                                                                                                                                                                                                                                                                                                                                                                                                                                                                                                                                                                                                                                                                                                                                                                                                                                                                                                                                                                                                                                                                                                                                                                                                                                                                                                                                                                                                                                                                                                                                                                                                                                                                                                                                                                                                                                                                                                                | Not applicable                                                                                                                                                                                     | No increase consistent with progression                                                                                                                                                                                                                                                                                                                                                                                                                                    |
| Organ enlargement                                                                                                                                                                                                                                                                                                                                                                                                                                                                                                                                                                                                                                                                                                                                                                                                                                                                                                                                                                                                                                                                                                                                                                                                                                                                                                                                                                                                                                                                                                                                                                                                                                                                                                                                                                                                                                                                                                                                                                                                                                                                                                                                                                                                                                                                                                                                                                                                                                                                  | Not applicable                                                                                                                                                                                     | No increase consistent with progression                                                                                                                                                                                                                                                                                                                                                                                                                                    |
| New lesions                                                                                                                                                                                                                                                                                                                                                                                                                                                                                                                                                                                                                                                                                                                                                                                                                                                                                                                                                                                                                                                                                                                                                                                                                                                                                                                                                                                                                                                                                                                                                                                                                                                                                                                                                                                                                                                                                                                                                                                                                                                                                                                                                                                                                                                                                                                                                                                                                                                                        | None                                                                                                                                                                                               | None                                                                                                                                                                                                                                                                                                                                                                                                                                                                       |
| Bone marrow                                                                                                                                                                                                                                                                                                                                                                                                                                                                                                                                                                                                                                                                                                                                                                                                                                                                                                                                                                                                                                                                                                                                                                                                                                                                                                                                                                                                                                                                                                                                                                                                                                                                                                                                                                                                                                                                                                                                                                                                                                                                                                                                                                                                                                                                                                                                                                                                                                                                        | No change from baseline                                                                                                                                                                            | Not applicable                                                                                                                                                                                                                                                                                                                                                                                                                                                             |
